### Randomization and blinding

Patients will be randomized 1 day before surgery using blocked, stratified randomization by independent research staff to 1 of 2 treatment groups (the combined group or the control group) after study enrollment. We will randomize the patients in a 1:1 ratio in blocks of four. The randomized allocation list will be generated by using a real-time, online system on the day before surgery. The randomization results will be maintained by independent researchers who will not participate in any other work of this study to guarantee allocation blinding. The presence of moderate or severe preoperative pain will be used as a basis for the stratification of patients (evaluated by a visual analog scale, range: 0–100, with 0, no pain; 100, the worst pain; moderate or severe preoperative pain is defined by a VAS score equal to or more than 40 mm).

Allocation concealment will be achieved using study capsules and intravenous infusions with identical appearance for placebo and drugs. All the trial drugs will be provided by a medicine company (Hengrui Induction, Jiangsu, China) with no other contribution to this trial. The appearance of all trial capsules (placebo capsules containing starch and pregabalin capsules) will be the same. Esketamine will be diluted to a concentration of 0.5 mg/ml with normal saline. Colorless 50-ml syringes containing clear esketamine or placebo (normal saline) solution will be prepared in a blinded manner by an independent research assistant. The randomization code will be marked on the syringes and the drug bottles of the study capsules. Only the study investigator who assigns participants to interventions will be unblinded to the treatment assignment. All other study researchers will be blinded to the treatment assignment, including responsible anesthesiologists and the neurosurgeons in charge of the patients, the outcome assessors, data analysts, and other relevant investigators.

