**Fig. 2 Fig2:**
[figure not shown]
Standard Protocol Items: Recommendations for Interventional Trials (SPIRIT) figure showing the schedule of enrollment, intervention, and assessments

Secondary outcomes include the following:Acute pain assessment: the maximal VAS score (when the patients felt the most intense pain over the last 24 h before being interviewed) 0–2 h, 2–24 h, 24–48 h, 48–72 h after leaving the operating room and 24 h before discharge; the incidence of acute moderate-to-severe postsurgical pain at each other time point (defined as the VAS score ≥ 40 mm)Subacute or chronic pain assessment: The incidence of postsurgical pain was assessed by a number rating scale (NRS: 0~10) at 1 month and 3 months (defined as an NRS score > 3)Neuropathic pain assessment: the short-form McGill pain questionnaire-2 (SF-MPQ-2) scores at 1 month and 3 months postoperativelyTotal opioid consumption within the 48 h period after surgeryEffective or noneffective button presses for PCIAQuality of anesthesia emergence evaluated by a 15-item quality of recovery scale (QoR-15) on POD3 and at dischargeThe incidence of psychotic side effects (such as hallucinations and dissociative symptoms) was determined using the Brief Psychiatric Rating Scale (BPRS) and Clinician-Administered Dissociative States Scale (CADSS) at 2 h after surgery, POD1, POD2, and POD3Adverse events included drug-related (palpitation, hypertension, dizziness, diplopia) and operation- or anesthesia-related complications, the incidence of PONV, and the incidence of postsurgical delirium at 2 h after surgery, POD1, POD2, and POD3Other outcomes: perioperative depressive/anxious symptoms assessed by the Patient Health Questionnaire 9 (PHQ-9) and Generalized Anxiety Disorder scale (GAD-7) on POD3, at discharge, and 1 month and 3 months after surgery

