### Statistical analysis

Continuous data will be described as the mean with standard deviation (SD) or median with interquartile range (IQR) based on its distribution. The histogram and Kolmogorov–Smirnov tests will be used to evaluate the normality of the data distribution. Categorical variables will be summarized as counts and percentages. The primary outcome is categorical and will be analyzed by using the chi-square test or Fisher’s exact test. Regarding the secondary outcomes, based on the type of each variable, the difference between groups will be analyzed using *t* tests, Mann–Whitney *U* tests, and chi-square or Fisher’s exact tests as appropriate. We will use the modified intension-to-treat (mITT) analysis to report our results, and we will use per-protocol (PP) analysis to perform the sensitivity analysis. The methods for estimating effects and 95% CIs will be reported in our outcomes. Sensitivity analyses will be applied to determine the statistical nature of the missing data. A two-sided *P* value of 0.05 was considered statistically significant for the primary outcome. Because of the repeated measurement, the Holm–Bonferroni method will be used to adjust the *P* value for secondary outcomes. Statistical analysis will be implemented using SPSS version 23.0 software and Stata version 14.0.

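### Maximal VAS is compared without adjusting for preoperative VAS, which is scored in every patient and used for stratification: valid, but a modest loss of precision on a secondary outcome

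*Protocol article*

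**What the plan says.** Three parts of the Protocol article bear on this.

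- **Randomization and blinding.** "The presence of moderate or severe preoperative pain will be used as a basis for the stratification of patients", and "moderate or severe preoperative pain is defined by a VAS score equal to or more than 40 mm". The score is on a 0–100 scale. Allocation follows within strata: "We will randomize the patients in a 1:1 ratio in blocks of four". Every randomized patient must therefore have a preoperative VAS.
- **Outcomes, secondary outcomes.** The list opens with the maximal VAS score at "0–2 h, 2–24 h, 24–48 h, 48–72 h after leaving the operating room and 24 h before discharge", which makes five windows.
- **Statistical analysis.** For secondary outcomes, "the difference between groups will be analyzed using *t* tests, Mann–Whitney *U* tests, and chi-square or Fisher’s exact tests as appropriate". No covariate, stratum term or repeated-measures model is named. The repeated windows are dealt with only through multiplicity: "Because of the repeated measurement, the Holm–Bonferroni method will be used to adjust the *P* value for secondary outcomes".

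**The concern.** The investigators thought preoperative pain prognostic enough to stratify on, but the stated analysis of the matching postoperative score ignores it. Two things follow if the two scores are correlated.

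1. Variation between patients that preoperative VAS could explain stays in the error term, so the treatment difference is estimated less precisely than the data allow.
2. Stratified blocks balance the arms on a dichotomised version of that same score. The real sampling variation of the mean difference is then smaller than the two-sample t test assumes, so the test runs below its nominal level.

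At stake is how well the trial can show the size and timing of any analgesic effect, which a single yes/no outcome over 48 h cannot show. Information is scarce here: about 36 evaluable patients per arm, with a Holm–Bonferroni correction on top. The primary test is not part of this point.

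**Working it through.** **Inputs from the article.** 90 patients, 1:1, 20% withdrawal, blocks of four, stratified at VAS ≥ 40 (Sample size calculation; Randomization and blinding). Evaluable: 90 × 0.8 = 72, or 36 per arm.

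**Inputs not in the article.** No SD, effect size or correlation is stated for maximal VAS, so there is no design figure to reproduce for this outcome. The following are assumptions: rho of 0.2, 0.3 and 0.5; a shift of 0.5 SD; and, for the type I error, 40% of patients in the upper stratum with loss at random.

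**Step 1: interval width.** In SD units the unadjusted standard error is √(2/36) = 0.236, so the 95% half-width is 1.96 × 0.236 = 0.46 SD. ANCOVA multiplies this by √(1 − rho²).

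| rho | √(1 − rho²) | half-width (SD) | narrower by |
|---|---|---|---|
| 0.2 | 0.980 | 0.45 | 2% |
| 0.3 | 0.954 | 0.44 | 5% |
| 0.5 | 0.866 | 0.40 | 13% |

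**Step 2: power for a 0.5 SD shift.** Noncentral t, noncentrality = d/√(1 − rho²) × √(36/2), with 70 degrees of freedom unadjusted and 69 adjusted.

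| | noncentrality | two-sided 0.05 | two-sided 0.01 |
|---|---|---|---|
| unadjusted | 2.12 | 55% | 31% |
| rho 0.2 | 2.17 | 57% | 32% |
| rho 0.3 | 2.22 | 59% | 34% |
| rho 0.5 | 2.45 | 68% | 43% |

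The 0.01 column is the first Holm step if the family is exactly the five windows (0.05/5). The article does not define the family.

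**Step 3: a larger shift.** If the planned 60% and 30% at VAS ≥ 40 are read as a shift between normal scores with equal SD, d = 0.253 + 0.524 = 0.78 SD. At 0.05, power is 90% unadjusted, against 91%, 93% and 96% at rho 0.2, 0.3 and 0.5. At 0.01 it is 74%, against 76%, 79% and 87%.

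**Step 4: type I error of the t test.** In simulation, 90 patients were randomized in stratified blocks of four, 18 were lost at random, and there was no treatment effect. With 20,000 runs per setting, the t test rejected in 4.5% (rho 0.2), 4.6% (rho 0.3) and 3.7% (rho 0.5) of runs at nominal 5%. ANCOVA gave 4.7%, 5.2% and 5.1%. At rho 0.5 the t test's average reported standard error was 0.236 against a true sampling SD of 0.222. Other runs with the same design gave 3.6% to 4.1% at rho 0.5.

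**Step 5: the rank-test branch.** With scores bounded to 0–100, rho 0.5, a 0.5 SD shift and alpha 0.05, simulated power was 55% for the t test, 52% for Mann–Whitney and 66% for ANCOVA. Moving to the rank test does not recover the loss.

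**Step 6: if rho is zero.** The ANCOVA standard error is 1.003 times the unadjusted one, so adjustment costs almost nothing when it does not help.

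**The case against.** The strongest reply is that this is a choice about efficiency and not an error. Unadjusted tests on randomized arms are valid, only secondary outcomes are affected, and a separate analysis plan may already contain an adjusted model. All of that stands, except that the article does name the tests, so as written this is a stated choice and not a detail left open.

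The correlation may also be low. Severe chronic pain and long-term analgesic use are excluded, which narrows the baseline range. All patients get PCIA and an NSAID, with rescue at VAS ≥ 40. The baseline score is not said to be a 24 h maximum, so scale and instrument match but the measure may not. This too stands, and it is why the low values of rho deserve as much weight as 0.5. The article's figure of nearly 80% among patients with preoperative pain (Sample size calculation) does not settle the matter: the Background cites the same reference for almost 80% of spinal surgery patients in general.

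A reader might infer more than the article supports:

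- **That the results would be biased or false positives inflated.** They would not; the error goes the conservative way.
- **That a real effect would be missed only for want of the covariate.** If the 0.78 SD shift held in a window, the t test would already have about 90% power at 0.05. That shift is itself borrowed from a primary outcome defined over the whole 48 h.
- **That the published intervals will certainly be too wide.** The Statistical analysis section leaves the interval method to be reported with the results.
- **That maximal VAS is the main secondary outcome.** It is listed first, but the secondary outcomes are not ranked.

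**Conclusion.** The point holds as a modest, avoidable loss of precision on a secondary outcome. The direction is certain for any non-zero correlation. The size is not, because the article gives no correlation: intervals 2% to 13% wider than they need be, taking ANCOVA at rho 0.2 to 0.5 as the reference for narrowing, and 2 to 12 or 13 points of power for an assumed 0.5 SD shift at 0.05 (55% against 57%, 59% and 68%). The t test's conservatism is negligible at rho 0.2–0.3 and reaches about 3.6–4% instead of 5% at rho 0.5, given 40% in the upper stratum and 20% random loss. The larger differences at alpha 0.01 depend on an assumed five-test Holm family and should not lead the argument. Because adjustment costs almost nothing even at rho zero, the change is worth making.

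**What to change.** Before unblinding, state in the Statistical analysis section that maximal VAS will be analysed with continuous preoperative VAS as a covariate and, if wished, the randomization stratum. Either form would do:

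- ANCOVA in each of the five windows; or
- a mixed model over the four fixed windows (0–2, 2–24, 24–48 and 48–72 h) with treatment, window, treatment-by-window, preoperative VAS and preoperative-VAS-by-window, plus a separate ANCOVA for the 24 h before discharge, whose timing differs between patients.

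Use a rank-based ANCOVA if scores are markedly skewed. Report adjusted differences with 95% CIs, retain Holm–Bonferroni, and keep the unadjusted t or Mann–Whitney tests as sensitivity analyses. Confirm that the preoperative score itself, and not only the stratum, is recorded.

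The cost is a few lines of text, one or two degrees of freedom in the per-window ANCOVA, and a slightly more complex model. No new visits or patients are needed, and SPSS and Stata, the packages named in the article, can fit these models.

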**Methods/design:**

This is a protocol for a randomized double-blind controlled trial to evaluate the effect of esketamine combined with pregabalin on postsurgical pain in spinal surgery. Patients aged 18 to 65 years scheduled for spinal neoplasm resection will be randomly allocated into the combined and control groups in a 1:1 ratio. In the combined group, esketamine will be given during the during the surgery procedure until 48-h postoperative period, and pregabalin will be taken from 2 h before the surgery to 2 weeks postoperatively. The control group will receive normal saline and placebo capsules at the same time points. Both groups received a background analgesic regimen by using patient-controlled intravenous analgesia (containing 100 μg sufentanil and 16 mg ondansetron) until 2 days after surgery. To ensure the accuracy and reliability of this trial, all the researchers and patients will be blinded until the completion of this study. The primary outcome will be the proportion of patients with acute moderate-to-severe postsurgical pain (visual analog scale, VAS ≥ 40, range: 0–100, with 0, no pain; 100, the worst pain) during the 48-h postoperative period. The secondary outcomes will include the maximal VAS scores (when the patients felt the most intense pain over the last 24 h before being interviewed) at 0–2 h, 2–24 h, 24–48 h, and 48–72 h after leaving the operating room and 24 h before discharge; the incidence of acute moderate-to-severe postsurgical pain at each other time point; chronic postsurgical pain assessment; neuropathic pain assessment; and the incidence of drug-related adverse events and other postoperative complications, such as postoperative delirium and postoperative nausea and vomiting (PONV).

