**Discussion:**

The aim of this study was to evaluate the effect of esketamine combined with pregabalin on acute postsurgical pain in patients undergoing resection of spinal neoplasms. The safety of this perioperative pain management strategy will also be examined.

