### Sample size calculation

According to a previous randomized controlled trial that investigated the effect of combined ketamine and pregabalin on persistent postoperative pain, the prevalence of moderate-to-severe acute postoperative pain at 24 h after surgery was 42% in the combined group and 78% in the control group [16]. Among patients with preoperative pain, the incidence of acute moderate-to-severe postsurgical pain in the population undergoing spinal surgery is nearly 80% [1]. Based on the above data and the current clinical situation, we estimate that the incidence of acute moderate-to-severe postsurgical pain will be 30% in the combined group and 60% in the control group, with a total 2-sided type I error rate of 0.05 and a 20% withdrawal rate. Ninety patients will have to be enrolled to achieve a statistical power of 80% (*P* values of 0.05).

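### The Holm–Bonferroni adjustment of secondary P values is not limited to efficacy, so moderate harms measured repeatedly may lose nominal significance

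*Protocol article*

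**What the plan says.** Three parts of the protocol article matter here.

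- **Statistical analysis.** The primary outcome stands alone: a two-sided P "value of 0.05 was considered statistically significant for the primary outcome". For the rest, "Regarding the secondary outcomes, based on the type of each variable, the difference between groups will be analyzed using" t, Mann–Whitney, chi-square or Fisher tests. Then: "Because of the repeated measurement, the Holm–Bonferroni method will be used to adjust the" P value for secondary outcomes. No outcome type is exempted and the family is not described. The same section promises counts and percentages for categorical variables, and effect estimates with 95% confidence intervals.
- **Outcomes.** One list, opened by "Secondary outcomes include the following", holds the pain, opioid, recovery and mood outcomes together with psychotic side effects (BPRS and CADSS at 2 h and on postoperative days 1, 2 and 3), drug-related and operation- or anesthesia-related adverse events, nausea and vomiting, and delirium. The abstract also names adverse events, delirium, and nausea and vomiting as secondary.
- **Safety.** The abstract states: "The safety of this perioperative pain management strategy will also be examined". The section on adverse event reporting and harms says that every adverse event will appear in the final report.

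**The concern.** Familywise control limits false claims of benefit. For harms the costlier error is usually the missed signal, and a Holm adjustment makes that error more likely. The rule as written reaches harm outcomes because they sit in the list to which it applies.

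This matters more here than in many small trials. Safety is a stated aim. The Background cites evidence that S-ketamine may raise psychotomimetic events. The Discussion expects the combination to prove safe as well as effective. No data monitoring board and no interim analysis are planned, so the final between-group comparison carries much of the safety evidence. If an adjusted non-significant P value were read as absence of harm, the adjustment itself would have helped to produce that reading.

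**Working it through.** The plan states no family size and no adjusted threshold, so there is no figure of its own to reproduce. The check measures what the stated rule does to a harm comparison.

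**Inputs from the protocol**
- Total 90, allocated 1:1, gives 45 per arm. With the planned 20% withdrawal, 45 × 0.8 = 36 per arm. The total is taken as given.
- Overall level for a family: 0.05, two-sided. The protocol states this level for the primary outcome; its use for the Holm family is assumed.

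**Inputs assumed**
- Family size m, counted from the Outcomes list:
  - m = 4: time points within one outcome (BPRS, CADSS or delirium).
  - m = 18: one test per outcome, with each of the four named drug-related events separate.
  - m = 40: scales at each time, other adverse events once.
  - m = 47: maximal VAS 5 + pain incidence 5 + NRS 2 + SF-MPQ-2 2 + opioid use 1 + PCIA presses 2 + QoR-15 2 + BPRS and CADSS 8 + drug-related events 4 + nausea and vomiting 4 + delirium 4 + PHQ-9 and GAD-7 8.
  - m = 63: every outcome at every time.
- Event counts and harm rates are illustrations. The protocol gives none.

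**Formula.** Holm's first step compares the smallest P value with 0.05/m, so the adjusted P is min(1, m × P). The thresholds are 0.0125 (m = 4), 0.0028 (18), 0.00125 (40), 0.0011 (47) and 0.0008 (63).

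**Fisher P values, and adjusted P at the first step**

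| Events | Unadjusted P | m = 4 | m = 18 | m = 47 | m = 63 |
|---|---|---|---|---|---|
| 9/36 vs 2/36 | 0.046 | 0.18 | 0.82 | 1.0 | 1.0 |
| 11/36 vs 2/36 | 0.0120 | 0.048 | 0.22 | 0.56 | 0.76 |
| 10/45 vs 2/45 | 0.027 | 0.11 | 0.48 | 1.0 | 1.0 |
| 12/45 vs 2/45 | 0.007 | 0.028 | 0.13 | 0.33 | 0.45 |
| 16/45 vs 2/45 | 0.0004 | 0.001 | 0.007 | 0.017 | 0.023 |

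Holm relaxes at later steps, so these are worst-case values. For 9/36 against 2/36 with m = 4, the second and third steps still give 3 × 0.0457 = 0.14 and 2 × 0.0457 = 0.09. The comparison passes only at the last step, after the other three time points have all been declared significant.

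**Power for an assumed harm of 5% against 20%, 45 per arm.** The normal approximation is Φ{[Δ√n − z√(2p̄(1−p̄))] / √[p₀(1−p₀) + p₁(1−p₁)]}, with Δ = 0.15, p̄ = 0.125 and z taken at 0.05/m, two-sided.
- Unadjusted: (1.006 − 1.960 × 0.468)/0.456 ≈ 0.197, power 58%.
- m = 4: (1.006 − 2.498 × 0.468)/0.456 ≈ −0.356, power 36%.
- m = 18, 40 and 63: 19%, 14% and 11%.

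Exact Fisher power is 48% unadjusted and 25%, 11%, 7% and 6% at m = 4, 18, 40 and 63. With 36 per arm the approximation gives 49% unadjusted and 28% at m = 4.

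**The case against.** **The single large family is a reading, not a fact.** A reader might infer that every secondary comparison enters one family of about 47 tests, with a first threshold near 0.001. The text does not say that all secondary outcomes form one family. Its stated reason, repeated measurement, fits adjustment across the time points of each outcome at least as well. At m = 4, 11/36 against 2/36 passes (0.048). The exact family is also something that an analysis plan commonly settles. This objection stands against any single figure. It does not remove the point, because BPRS, CADSS and delirium are each measured at four times and are adjusted on the narrow reading too.

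**Some adverse events may escape.** If only repeated outcomes are adjusted, and the listed assessment times attach only to delirium, then palpitation, hypertension, dizziness and diplopia may fall outside the rule. This stands; for those events the adjustment is possible, not established.

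**Harms are not hidden.** A reader might infer that real harms would be declared non-significant and that the plan biases the trial toward a finding of safety. The documents do not support this. The adjustment applies to P values and leaves estimates untouched; counts and 95% confidence intervals are planned, and all adverse events are to be documented. For 9/36 against 2/36 a Newcombe 95% interval for the risk difference runs from about 3 to 36 percentage points, so the signal would still show. Large harms keep their significance. What is affected is the formal call on moderate harms.

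**Separate tests by time point are not an error.** One might also want a single longitudinal model for the pain scores. That is a preference: it answers a question about an average effect, whereas the listed outcomes are specific to time windows, and tests by window with Holm are valid.

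**Conclusion.** The point holds in a limited form. The stated rule adjusts P values for secondary outcomes without an efficacy restriction, and harm outcomes are in that list. On every reading considered, at least BPRS, CADSS and delirium are adjusted. A moderate harm may then lose nominal significance: 9/36 against 2/36 moves from 0.046 to 0.18 on the narrowest reading and to 1.0 at 47 tests. For a harm of 5% against 20% with 45 per arm, approximate power falls from 58% to 36% at m = 4, and to between 19% and 11% for the wider families.

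These sizes rest on assumed family sizes, assumed event rates and the first, strictest Holm step. The undefined family adds to the difficulty, since the same safety data could give different calls depending on how it is later drawn. The primary analysis is not affected.

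**What to change.** In the Statistical analysis section, state that:

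1. Holm–Bonferroni applies only to the secondary efficacy outcomes, and say which comparisons form the family.
2. Safety outcomes (BPRS, CADSS, delirium, nausea and vomiting, adverse events) are reported unadjusted, with counts, risk differences and 95% confidence intervals, and are labelled descriptive.
3. No conclusion of safety will be drawn from an adjusted non-significant P value.

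The cost is a few sentences. Most of the reporting is already planned, and nothing changes for patients, data collection or sample size. The small downside is that some nominal safety differences will be chance findings, which is why the descriptive label is needed.
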